### Monitoring, safety and quality control

The study will be monitored in accordance with the local research and development department’s standard operating procedures to ensure compliance with The International Council for Harmonisation of Technical Requirements for Pharmaceuticals for Human Use (ICH) Good Clinical Practice (GCP) [30] and the Research Governance Framework 2005.

The collection and reporting of data on adverse events and serious adverse events will be in accordance with ICH GCP and the Research Governance Framework 2005. An adverse event (AE) is any untoward medical occurrence in a subject to whom a medicinal product or device has been administered as part of a research study, including occurrences which are not necessarily caused by or related to a medicinal product or device. An adverse reaction (AR) is any untoward and unintended response in a subject to a medicinal product or device. An adverse event becomes serious (SAE) if it results in death, is life-threatening, requires hospitalisation or prolongation of existing hospitalisation, results in persistent or significant disability or incapacity, is a congenital anomaly or birth defect or is otherwise considered medically significant by the investigator. The term ‘life-threatening’ refers to an event in which the patient was at risk of death at the time of the event; it does not refer to an event which hypothetically might have caused death if it were more severe.

Hospitalizations planned prior to enrolment in the trial (elective surgery) or for social reasons should not normally be considered as SAEs unless the hospitalisation has to be prolonged.

The AE reporting period for this trial begins as soon as patients have consented to the trial and ends at the point of discharge from the trial, following a final study visit or telephone consultation at 1 year following surgery. The health status of subjects will be checked at each study visit. The investigator will record all directly observed AEs and all AEs spontaneously reported by the trial subject. A pre-existing condition (i.e. a disorder present at the baseline study visit and noted on the baseline medical history/physical examination form/medical notes) is not to be reported as an AE unless the condition worsens or episodes increase in frequency during the AE-reporting period. All adverse events (serious and non-serious) will be recorded by the investigator in patient’s data collection forms (CRFs) using R&D’s adverse event report form. All adverse events will be recorded by the investigator in patients’ medical records/notes. All AEs will be followed-up by investigators until the event has resolved or a decision has been taken for no further follow-up.

If a clinically significant abnormal laboratory value occurs, this abnormality will be recorded as an adverse event/reaction.

The investigator will report fatal or life-threatening SAEs or serious adverse reactions (SARs) to the research ethics committee (REC) within 7 days and follow-up information within a further 8 days by following the request on the serious event initial and follow-up report forms. The investigator will send all other SAE or SAR reports to the REC within a maximum of 15 days.

Patients have access to information on the complaints procedure for obtaining compensation following harm through non-negligence or negligence as a result of participating in the trial.

Study completion refers to the date of final data collection from the last patient. Paper records from the trial will be stored for 5 years from trial end.

An end of study declaration form will be submitted to the REC and Trust R&D within 90 days from completion of the trial and within 15 days if the trial is discontinued prematurely. A summary of the trial report/publication will be submitted to the REC and Trust R&D within 1 year of the end of trial.

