### Blinding

Due to the nature of the treatment, a double-blind study is not possible (Leukomed® Sorbact® contains a coloured wound contact layer that is not present on standard dressings). To reduce the risk of bias, assessor reported outcomes, namely the ASEPSIS scoring of wounds, will be performed by a blinded assessor who will not have access to the patient notes. Anonymous photos of wounds will be rated by a third blinded assessor to reduce bias and ensure discrepancies in ASEPSIS scores are addressed. Bias in other outcomes will be limited by the use of predetermined objective measurements and bias in quality of life outcomes will be reduced by using patient-reported quality of life outcomes.

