## Discussion

Surgical site infections are now the second most common hospital acquired infections, and cost many thousands of pounds per patient per infection [31]. Any strategy for reducing this burden should be investigated. DACC-coated dressings show no evidence of antimicrobial resistance and have no documented cases of adverse reaction. The aim of the DRESSINg trial is to investigate the effectiveness of this novel preventative measure at reducing wound infections post-surgery.

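### No stated item asks about dressing reactions in the same way in both arms of a trial where patients and visit staff know the allocation; the adverse event (AE) definition and the start of AE reporting also need reconciling

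*Protocol article*

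**What the plan says.** Under Monitoring, safety and quality control, the article says "The health status of subjects will be checked at each study visit", and then sets the recording rule: "The investigator will record all directly observed AEs and all AEs spontaneously reported by the trial subject". It defines an AE as "any untoward medical occurrence in a subject to whom a medicinal product or device has been administered as part of a research study". The same definition makes clear that unrelated events count as well: "including occurrences which are not necessarily caused by or related to a medicinal product or device". Adverse reactions are defined as a separate category. On timing it says "The AE reporting period for this trial begins as soon as patients have consented to the trial".

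The Blinding section says "Due to the nature of the treatment, a double-blind study is not possible" and explains that the DACC dressing has a coloured contact layer that the control lacks. ASEPSIS scoring is assessor-blind.

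Under Study visits, a non-blinded nurse or doctor collects the visit information and removes the dressing. A second, blinded person then comes in to score the wound, and photographs are taken.

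The Discussion says that DACC dressings "have no documented cases of adverse reaction".

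**The concern.** A local reaction is a harm that a dressing could plausibly cause. Allergy to a component of either dressing is an exclusion criterion, and Trial exit allows for withdrawal after an adverse reaction. The article states what is recorded (what is seen and what is volunteered) but no uniform question. When patients know their dressing, a new coloured product may prompt more, or less, volunteering than a familiar one. Staff who know the arm may likewise look with different attention.

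The pilot's own aims are at stake. Withdrawal rates, reasons for drop-out, and whether the dressing suits different wounds and sites are all listed as feasibility outcomes. A comparison of reactions by arm could reflect reporting behaviour rather than the dressings. A low count would say little about the Discussion's statement on adverse reactions.

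A smaller matter is that the AE definition presupposes that a device has been administered, whereas the reporting period opens at consent.

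**Working it through.** The safety section gives no reaction rate, capture rate or safety sample size, so there is no plan figure to reproduce. The check is a comparison of the text, followed by an illustration.

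**1. When a reaction could appear, and when it would be seen.** The section on dressings and post-operative procedures schedules changes on day 2 and at the first wound review (days 5–7), allows interim changes where clinically indicated, and supplies like-for-like dressings after discharge until the wound heals, with instructions to community teams. Study visits are at days 5–7, day 30 and 6 months. A reaction present at a visit can be directly observed. One that appears and settles around a change between visits reaches the record, under the stated rule, only if somebody reports it.

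**2. Who looks and who asks.** The visit items listed under Study visits include antibiotics, length of stay, GP visits, dressing changes and numbers, and return to activities. The list is given as examples, and no reaction item is among them. The blinded assessor sees the exposed wound, but the only stated task is the ASEPSIS score.

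**3. Illustration.** Equal allocation of 144 gives 144/2 = 72 per arm, taking full retention. Let p be the true reaction rate and c the share captured; both are assumed. The chance of at least one recorded reaction in an arm is 1 − (1 − p·c)^72:

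| Capture c | p = 1% | p = 2% | p = 5% |
|---|---|---|---|
| 100% | 0.515 | 0.767 | 0.975 |
| 75% | 0.418 | 0.663 | 0.936 |
| 50% | 0.303 | 0.515 | 0.838 |

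If no reaction is recorded among 72, the one-sided 95% upper limit for the recorded rate is 1 − 0.05^(1/72) = 0.041. If only half were captured, the limit for the true rate would be 0.041/0.5 = 0.082.

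Uneven capture carries straight into the comparison, because the ratio of expected counts is (p·c₁)/(p·c₂) = c₁/c₂. With p = 5% in both arms, capture of 100% against 50% gives 72 × 0.05 = 3.6 against 72 × 0.05 × 0.5 = 1.8 expected recorded reactions, although the arms do not differ.

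**4. Start of the period.** Table 1 places consent at the baseline visit and randomisation on day 0. The first dressing follows the operation. An event between consent and first dressing is inside the reporting period but outside the AE definition, so two investigators following the text could count differently. Events before randomisation cannot depend on arm, and the early start loses none.

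**The case against.** The strongest reply is that capture is not merely passive. Health status is checked at each visit, the dressing comes off, a blinded assessor inspects the wound, and photographs are taken. The list of visit items is not exhaustive. Table 1 schedules a wound-healing questionnaire at day 30 and 6 months whose items are not shown. AEs go on the R&D department's own form, and a condensed article may leave prompts and attribution fields to such documents. This largely stands: it rules out saying that AEs are captured only by chance observation or volunteering. It does not remove the point, because the article does state a capture rule, and nothing it describes asks both arms about reactions in the same way.

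A reader might infer four stronger things, and the documents support none of them:

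- *That reactions are under-recorded.* No capture rate is given, so this is a possibility and not a finding.
- *That starting at consent causes under-recording.* It can only add events, and those before the first dressing can be separated by date.
- *That mixing dressing reactions with surgical events is an error.* The AE definition includes unrelated occurrences on purpose, adverse reactions are a separate category, and post-operative complications would count in any case.
- *That the long interval between the day 30 and 6-month visits is a serious safety gap.* Trial dressings are used only until healing, so for healed wounds the interval falls after exposure.

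It is also fair to say that no listed clinical outcome concerns dressing reactions, and that the Discussion's statement is background, not a hypothesis under test.

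**Conclusion.** The point holds as a modest design weakness. Under the stated rule, dressing reactions may be recorded incompletely and unevenly by arm, mainly those at changes between visits. The size cannot be derived from the documents. The figures above rest on assumed reaction rates of 1–5%, assumed capture of 50–100% and 72 evaluable patients per arm. They show only that incomplete capture would matter most for uncommon reactions, and that uneven capture could produce an apparent difference between arms.

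The mismatch between the AE definition and the start of reporting is a genuine conflict in the text, but minor. It affects consistency of counting and gives no bias between arms before randomisation.

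**What to change.** 1. Have the existing blinded assessor record skin reaction in the dressing area (yes/no, and type) at the day 5–7 and day 30 reviews, next to the ASEPSIS score, while the dressing is already off.
2. Ask both arms one identically worded question at each study visit: any reaction to the dressing, or stopping its use, since the last visit. The nurse or doctor who removes the dressing can ask it before the blinded assessor enters, so that the answer does not reveal the arm.
3. Reconcile the AE definition with the reporting period. If recording from consent is kept, say so in the definition and list events before the first dressing separately.

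The cost is one or two lines on the case report form and a wording correction, with no extra visit or staff. The small downside is that more minor skin events will be recorded.

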## Discussion

Surgical site infections are now the second most common hospital acquired infections, and cost many thousands of pounds per patient per infection [31]. Any strategy for reducing this burden should be investigated. DACC-coated dressings show no evidence of antimicrobial resistance and have no documented cases of adverse reaction. The aim of the DRESSINg trial is to investigate the effectiveness of this novel preventative measure at reducing wound infections post-surgery.

## Trial status

The DRESSINg trial pilot phase began recruiting in January 2017 and is currently in active recruitment.

## Abbreviations

AE: Adverse event
AR: Adverse reaction
CRF: Case report form
CSH: Cell surface hydrophobicity
DACC: Dialkylcarbamoylchloride
EQ-5D: EuroQol 5 domains
GP: General practitioner
HPA: Health protection agency
HYMS: Hull York Medical School
ICF: Informed consent form
MCA: Mental Capacity Act
R&D: Research and development
REC: Research ethics committee
SAE: Serious adverse event
SAR: Serious adverse reaction
SSI: Surgical site infection
UK: United Kingdom
